## Abstract

**Background:**

Hemorrhage from intra-abdominal injuries (IAI) is a leading cause of traumatic deaths in children. Concern over misdiagnosing IAIs has resulted in excessive use of abdominal computed tomography (CT). Despite its many benefits, CT presents risks to children most notably radiation-induced malignancies. Thus, we must safely limit abdominal CT evaluation to those at non-negligible risk. The focused assessment with sonography for trauma (FAST) examination uses abdominal ultrasonography to detect the presence of intraperitoneal fluid in injured patients and may decrease abdominal CT use in some children. Limited and conflicting data exists on the utility of the FAST examination in children. A large multicenter study is thus necessary to determine if the FAST examination should routinely be included in the diagnostic evaluation of injured children.

**Methods:**

This is a multicenter, randomized controlled clinical trial to assess the impact of the FAST examination on the initial evaluation of children with blunt abdominal trauma. Enrolled participants will be randomized 1:1 to the FAST examination plus routine care or routine care alone during their initial emergency department (ED) evaluation. The study will enroll 3194 (initial sample size) to 4346 (second sample size) children at six diverse sites. The primary outcomes are as follows: (1) The proportion of abdominal CT in the initial 24 h of care and (2) the proportion of missed or delayed diagnoses of IAIs. Secondary outcomes include (1) ED length of stay, (2) hospitalization proportion and length of hospital stay, (3) physician suspicion of IAI, (4) the proportion of abdominal CT use in the subgroup of children 0 to 3 years old, and (5) laparotomy proportion. Hospitalized participants will be followed through their stay, and guardians of those discharged from the ED will be contacted after 1 week to assess their status.

**Discussion:**

The study will determine if the FAST examination results in a safe reduction of CT use in injured children and will provide definitive evidence if the FAST examination should be routinely implemented in the initial evaluation of children with blunt abdominal trauma.

**Trial registration:**

ClinicalTrials.gov NCT05910567. Registered on May 9, 2023

**Supplementary Information:**

The online version contains supplementary material available at 10.1186/s13063-025-09137-6.

## Introduction

### {#6a Background and rationale}

Hemorrhage from intra-abdominal injuries (IAI) is a leading cause of traumatic deaths in children [1]. Therefore, several consensus panels have placed the management of injured children as a research priority [2–4]. Many children with IAIs have subtle symptoms, making the diagnosis difficult, and missed or delayed diagnoses increase morbidity [5–8]. Excessive use of computed tomography (CT), however, also poses important risks, especially ionizing radiation exposure. CT is accurate in diagnosing IAIs, decreases the level of clinical monitoring required, and is important for determining the need for intervention including surgical treatment [9, 10]. However, due to the risks of radiation-induced malignancies [11–21], the use of CT should be optimized. Point-of-care ultrasonography has been proposed as a method to optimize CT use [22].

The focused assessment with sonography for trauma (FAST) examination uses abdominal point-of-care ultrasonography to detect intraperitoneal fluid in injured patients [23, 24]. The use of the FAST examination evolved in injured adult patients. Two randomized controlled trials in adults demonstrated that an evaluation strategy incorporating the FAST examination improves several aspects of patient care, including safely decreasing abdominal CT use [25, 26]. There are compelling reasons to thoroughly evaluate injured children for IAIs; however, avoiding CT evaluation in those at low risk is also critical. The FAST examination is clinically indicated in hemodynamically unstable, injured children; it also may enhance the diagnostic evaluation and decrease the frequency of CT use in low-risk children. However, the data are limited on the utility of the FAST examination in stable pediatric trauma patients [27–31]. A large, multicenter, observational study suggests that the FAST examination safely decreases CT use in children at low risk for IAI [31]. However, a separate observational study suggests that “a negative FAST aids little in decision-making,” in injured children, questioning its routine use [27]. Furthermore, a single-center, randomized controlled trial of FAST in injured children at low (~5%) risk for IAI conducted by our group demonstrated no difference in the frequency of CT use in the FAST versus the non-FAST study arms [28]. That trial demonstrated, however, that physician suspicion of IAI significantly decreased after a negative FAST examination, but this post-FAST decrease in suspicion did not decrease CT use [28]. Finally, a 2021 meta-analysis suggests the FAST examination may decrease CT use but only in the lowest risk children [30]. The conflicting results from these studies strongly indicate the need for a multicenter clinical trial powered to answer this critical question definitively.

### {#7 Objectives}

The study’s primary objective is to determine the impact of the FAST examination on clinical care in hemodynamically stable children with blunt abdominal trauma.

Finally, as part of this study, we will attempt to identify patient, clinician, and system factors associated with obtaining abdominal CT scans in patients considered low risk for IAI by the clinician and who also have a negative FAST examination. This planned analysis will be conducted only on those patients in the FAST study arm. To obtain clinician factors, we will survey all eligible clinicians prior to their participation in the study. Specifics on this sub-aim are not described in this protocol manuscript.

### {#8 Trial design}

This is a multicenter randomized controlled, superiority trial.

## Methods: participants, interventions, and outcomes

### {#9 Study setting}

We will perform this study in the Pediatric Emergency Care Applied Research Network (PECARN), a national pediatric emergency care research network with a long history of successful multicenter studies, especially randomized controlled trials and studies in injured children. The six participating centers are geographically diverse with a heterogeneous patient population. Participating EDs include the following: the University of California, Davis (Sacramento, CA, USA), the Children’s Hospital Colorado (Denver, CO, USA), Cincinnati Children’s Hospital Medical Center (Cincinnati, OH, USA), Children’s Healthcare of Atlanta — Egleston Pediatric Hospital (Atlanta, GA, USA), Nationwide Children’s Hospital (Columbus, OH, USA), and the University of Texas Southwestern Medical Center (Dallas, TX, USA). All sites are urban, academic centers with dedicated pediatric EDs serving as level 1 pediatric trauma centers, including dedicated trauma teams composed of emergency medicine physicians, pediatric surgeons, and trauma surgeons.

### {#10 Eligibility criteria}

Children up until their 18th birthday will be assessed for eligibility as (1) this is the age range evaluated by most pediatric EDs and the age range in the single-center randomized trial [28], and (2) mechanisms and injury responses are different in those older than 18 years. Inclusion and exclusion criteria are designed to enroll a hemodynamically stable population with approximately 5% having IAI. This is because a prior study suggests that use of the FAST examination safely decreases abdominal CT use in those children considered to have a 1 to 10% risk of IAI [31]. Furthermore, a meta-analysis of the FAST examination in injured children suggests that CT may be avoided in low-risk children with normal FAST examinations; however, the FAST should not be used to rule out injury in children at higher risk [30]. Inclusion and exclusion criteria follow the same criteria used in the prior single-center randomized controlled trial of FAST in children in which 5.4% had IAIs and are presented in Table 1 [28].

**Table 1 Tab1:** Inclusion and exclusion criteria

Inclusion criteria [28]:
• Blunt torso trauma from a significant mechanism of injury:
◦ Motor vehicle collision:> 60 mph, ejection, or rollover
◦ Automobile (>25 miles/hour) versus pedestrian/bicycle
◦ Falls greater than 20 feet in height
◦ Crush injury to the torso or assault to the abdomen
• Glasgow Coma Scale score of 9-14 with blunt torso trauma
• Blunt traumatic event with extremity paralysis or multiple long bone fractures, regardless of the mechanism
• History and physical examination suggestive of abdominal injury following blunt torso trauma of any mechanism
Exclusion criteria [28]: Patients will be excluded for:
• Age-adjusted hypotension
◦ Prehospital or initial emergency department age-based hypotension. [57]
• Initial Glasgow Coma Scale score of 8 or less
• Penetrating trauma: Patients who are victims of stab or gunshot wounds
• Traumatic injury occurring more than 24 hours prior to the time of presentation to the emergency department
• Transfer of the patient with an abdominal CT scan, FAST examination or laparotomy previously performed
• Patients with known disease processes resulting in intraperitoneal fluid including liver failure and the presence of ventriculoperitoneal shunts

Hemodynamically unstable injured children are excluded as immediate FAST is recommended [32, 33]. Thus, equipoise on FAST use does not exist in children who are hypotensive/severely injured after blunt abdominal trauma.

### {#26a Who will take informed consent?}

Informed consent of the guardians for follow-up via email, telephone, or texting will be obtained by trained research coordinators and clinicians who provide care at the ED visit. Provider enrollment without research coordinator help has been successful in many PECARN studies.

### {#26b Additional consent provisions for collection and use of participant data and biological specimens}

This trial does not involve the collection of biological specimens. Secondary analyses and manuscripts are anticipated from the data collected, including the use of ultrasound for identifying pneumothoraces in children (eFAST) and the use of machine learning to interpret FAST images.

## Interventions

### {#6b Explanation for the choice of comparators}

Due to the clinical equipoise around the use of FAST in stable injured children, this trial will compare the FAST examination plus routine care versus routine care alone.

### {#11a Intervention description}

Bedside FAST examinations will be performed by the ED physicians providing care to the participants randomized to the FAST arm. Only ED physicians credentialed in the FAST examination will participate in the study. The FAST examinations will be performed using a portable ultrasound machine with low-frequency curvilinear or phased array probes (appropriate for patient size). Credentialing will follow guidelines for competency in point-of-care ultrasound established by the American College of Emergency Physicians, including the following: (1) understanding indications, (2) ability to obtain adequate images, and (3) correctly interpreting these images [34].

The intervention follows the FAST protocol for the detection of intraperitoneal fluid. This protocol includes views of Morison’s pouch (right upper quadrant), splenorenal fossa (left upper quadrant), and long and short axis of the pelvis and the heart. Images of extended-FAST (lung views) will not be required, but whether they are obtained by the physician will be collected on the case report form. No attempts to image the solid organs are required for the protocol, as this is not routine in the FAST examination. Clinicians are asked to record the results of the FAST examinations on the ultrasound machine as soon as the images are obtained. When possible, these FAST examination images will be uploaded via secure medical center Wi-Fi interface and stored on an IT-managed hospital secure server. Deidentified images will be uploaded into the Research Electronic Data Capture (REDCap) database. In some cases, the images will not be able to be saved and will no longer be available for storage and future review.

ED physicians (faculty or fellow physicians) caring for the participants will make bedside interpretations and record them onto case report forms. For analysis, FAST examinations will be classified as positive if any intraperitoneal fluid is identified (Fig 1.) or negative if no such fluid is noted (Fig. 2). The ED physician will also document the location of the fluid, if positive. We will not collect data on incidental findings or specify how treating physicians evaluate any findings that they may incidentally identify. Clinical action based on FAST findings will be at the discretion of the treating physicians.

**Fig. 1 Fig1:**
[figure not shown]
FAST image of the right upper quadrant view: The hypoechoic (black) area between the liver and renal parenchyma (arrow) is hemoperitoneum. This FAST is positive.

**Fig. 2 Fig2:**
[figure not shown]
FAST image of the right upper quadrant view. No fluid is found between the liver and renal parenchyma (arrow). This FAST is negative

All saved FAST examinations will also be presented for interpretation at each site per their quality improvement process to an expert ED ultrasonographer, unblinded to the initial interpretation. This person will be fellowship-trained in ED ultrasound and different from whom performs the study FAST examination. A separate study radiologist/ultrasonographer at the UC Davis Data Coordinating Center will review all FAST examinations in two circumstances: (1) ED physician interprets the FAST as negative for intraperitoneal fluid, and the site’s expert interprets it as positive, and (2) ED physician interprets the FAST as positive for intraperitoneal fluid, and the site’s expert interprets it as negative. If the UC Davis Data Coordinating Center expert agrees with the study site’s expert, the ED physician performing/interpreting the FAST examination will be informed that they misinterpreted it. The individual site leader will notify the ED physician of the discrepancy. This will not occur in real time.

### {#11b Criteria for discontinuing or modifying allocated interventions}

Based on perceived clinical necessity, the faculty physician caring for a patient in the non-FAST arm may perform a FAST examination. This would only be expected, however, in unusual cases such as the patient becoming hypotensive after randomization. This will be permitted by study protocol, as we cannot ethically interfere with patient care needs perceived by the faculty physician. We expect, however, that this will occur uncommonly (2.6% of cases in the single-center trial) [28].

### {#11c Strategies to improve adherence to interventions}

Adherence to randomization allocation is monitored monthly. Monthly compliance reports are sent to all participating sites, and compliance is discussed at each monthly call. Those sites whose allocation compliance falls below 95% have additional discussion and monitoring.

### {#11d Relevant concomitant care permitted or prohibited during the trial}

The study does not restrict care and interventions permitted during the trial.

### {#30 Provisions for posttrial care}

All participants will receive care as recommended by their care providers. No provisions for posttrial care beyond the standard care recommended are provided.

### {#12 Outcomes}

Primary outcomes will be measured and documented in both study arms. These outcome measures are the same as those used in the single-center randomized controlled trial. The primary outcomes are the abdominal CT proportion and the proportion of missed/delayed diagnosis of IAIs. The abdominal CT proportion will be calculated as the number of participants receiving abdominal CT scans in the initial 24 h divided by the number of participants in each arm (i.e., proportion of participants undergoing CT during their initial ED evaluation). Abdominal CT scans will be obtained at the discretion of the treating physicians in the ED. The other primary outcome is missed or delayed diagnosis of IAI. A missed diagnosis of IAI is defined as a diagnosis of IAI made after the patient is discharged from the hospital (if admitted) or from the ED (if not admitted to the hospital). A delayed diagnosis of IAI is defined as a diagnosis made after patient transfer from the ED to the hospital (including ward/intensive care unit bed). A delayed diagnosis may only be identified in a patient admitted to the hospital. Complications due to the missed/delayed diagnosis will be collected. We anticipate missed/delayed diagnoses to be rare but will nonetheless carefully assess for these as the FAST examination will require acceptance by clinicians that important injuries will not be missed if it is to be incorporated into practice.

Secondary outcome measures will also be collected and analyzed in both study arms. Although these outcomes are not the focus of the analysis, they will be gathered as they are important for assessing the utility of a pediatric trauma evaluation strategy using the FAST. Secondary outcomes include the following: (1) ED length of stay, (2) time to CT, (3) proportion of participants hospitalized and length of hospital stay, (4) proportion with abdominal CTs obtained in the subgroup of children 0 to 3 years old, (5) laparotomy proportion, and (6) physician suspicion of IAI.

ED length of stay is a continuous variable defined as the time (minutes) from ED arrival to ED disposition (ED discharge, hospital admission orders written, transfer to operating suite, or death). Abdominal CT time is defined as the start of the CT, and laparotomy time is defined as the time of entering the operating suite. Both of these are continuous variables and will be measured and compared as such. Time to CT or laparotomy will be measured from the time of ED arrival.

The hospitalization proportion is the number of participants hospitalized in each study arm divided by the number of participants in each arm (proportion admitted to the hospital from the ED). Participants will be considered hospitalized if they meet any of the following: (1) Admitted to observation status, (2) admitted to the intensive care unit or ward, and (3) transported from the ED to the operating suite/interventional radiology. We will also measure the length of stay for those hospitalized. This will be a continuous variable measured in hours from the time of ED arrival to discharge from the hospital or death in the hospital.

The proportion of abdominal CT use in children 0 to 3 years old is the number of abdominal CT scans performed in each study arm divided by the number of participants in each arm (proportion of participants undergoing an abdominal CT during their initial ED evaluation) among the population 0 to 3 years old. Laparotomy proportion is a binary indicator for whether the patient underwent a laparotomy or laparoscopy to identify/repair an IAI.

In those participants who undergo the FAST examination, we will also measure the impact of the FAST on the clinicians’ subsequent assessments of risk of IAI. In all participants, regardless of randomization, we will ask if the clinician believes the patient should have an abdominal CT scan and will measure clinician suspicion of IAI (classified by the clinician as < 1%, 1 to 5%, 6–10%, 11–50%, and over 50%). In those who are randomized to the FAST examination, the clinician will, after the FAST examination, again document if they believe the patient should have an abdominal CT and their suspicion of IAI (with the same categories). Finally, the clinician will, after performing the FAST examination, document if the FAST changed their suspicion for IAI or plans for patient evaluation or management.

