All analyses will account for site, sex, and age stratum differences. Baseline demographic (including age and sex), clinical and laboratory data, and outcome measures will be compared between the two cohorts (FAST versus the no-FAST study arms) using appropriate bivariable statistical methods to assess for parity between arms for known confounding variables (e.g., mechanism of injury, PECARN Abdominal Prediction Rule variables). Ninety-five percent CIs will be calculated for all measures of interest. All tests will be based on two-tailed alternatives. *P*-values < 0.05 will be considered statistically significant and adjusted for interim analyses. Categorical data will be compared using Cochran-Mantel–Haenszel risk difference testing and estimation method for stratified samples, using the Miettinen-Nurminen (score) confidence limits available in SAS for the common risk difference. McNemar chi-squared test will be used to compare differences in proportions between clinician suspicion of intra-abdominal injury before and after the FAST examination. Clinician suspicion will additionally be collapsed and compared into those with less than 1% suspicion and those with 1% or greater suspicion of IAI.

All continuous data will be assessed using nonparametric statistical analysis procedures for stratified data, with hypothesis testing using the Wilcoxon-Mann–Whitney procedure on outcomes that have been rank-aligned by stratum using the Hodges-Lehman estimator, a more powerful alternative to the van Elteren test [39]. ED length of stay and time to abdominal CT are continuous variables measured in minutes. We will compare ED and hospitalization lengths of stay between participants in the two study arms using nonparametric methods (described above). Hospitalization and laparotomy proportions are categorical variables (yes/no) and will be compared using methods described above for categorical variables.

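### Hospital stay and time to CT have values only for children admitted or scanned, so their between-arm tests compare subsets formed after randomization

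*Protocol article*

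**What the plan says.** The Outcomes section (item 12) of the protocol article lists hospital length of stay and time to CT as secondary outcomes.

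- **Hospital stay.** "We will also measure the length of stay for those hospitalized". The scale follows: "This will be a continuous variable measured in hours from the time of ED arrival to discharge from the hospital or death in the hospital". No value is given to a child sent home from the ED.
- **Time to CT.** "Abdominal CT time is defined as the start of the CT", and "Time to CT or laparotomy will be measured from the time of ED arrival". Of the CT and laparotomy times the section says: "Both of these are continuous variables and will be measured and compared as such". An unscanned child has no value.
- **Hospitalization** is itself an outcome with everyone in the denominator: "The hospitalization proportion is the number of participants hospitalized in each study arm divided by the number of participants in each arm".

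The statistical methods (item 20a) plan "hypothesis testing using the Wilcoxon-Mann–Whitney procedure on outcomes that have been rank-aligned by stratum" for continuous data, and add: "We will compare ED and hospitalization lengths of stay between participants in the two study arms using nonparametric methods". They mention no censoring, no competing event, and no rank or value for children who are not admitted or not scanned. The sentence on analyzing all randomized patients is attached to the primary analysis.

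**The concern.** Being scanned is a primary outcome, and being hospitalized is a secondary one. Conditioning on either selects children by something that happens after randomization and that the allocation may influence.

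The article's own evidence suggests that any effect on CT would be selective. Its Discussion cites relative risks of CT of 0.81 and 0.85 with FAST in children at 1–5% and 6–10% risk, and its eligibility section says FAST should not be used to rule out injury at higher risk. If FAST works as hoped, the scanned FAST children would be a higher-risk group than the scanned controls. A difference in scan times could then arise although no child was scanned earlier or later.

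For admission, the article states no expected effect. An effect in either direction is plausible: the Background says CT reduces the monitoring a child needs, and observation status counts as hospitalization. If FAST averted short observation stays, the remaining FAST admissions would be longer on average, and a benefit would read as a cost.

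**Working it through.** **1. The plan's own figure.** Inputs from the sample size section (item 14): 34% versus 30% CT use, 80% power, four stages; two-sided 0.05 from item 20a.

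Fixed-design n per arm = (1.960 + 0.842)² × (0.34×0.66 + 0.30×0.70) / 0.04² = 7.849 × 0.4344 / 0.0016 ≈ 2131, or 4262 in total. A four-look O'Brien-Fleming-type design inflates this by about 1.02, giving about 4347 against the stated 4346. The figure is sound and supplies the size of the scanned groups.

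**2. Who has a CT time.** With 4346/2 = 2173 per arm: control 0.34 × 2173 ≈ 739, FAST 0.30 × 2173 ≈ 652. The test uses (739 + 652)/4346 ≈ 32% of those randomized, in unequal subsets.

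**3. Hospital stay (assumed inputs).** 40% of controls are hospitalized. FAST averts 4 points of 12-hour stays. All other stays average 60 h and are unchanged.

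- Mean among the hospitalized, control: (0.36×60 + 0.04×12)/0.40 = 22.08/0.40 = 55.2 h. FAST: 60.0 h. FAST looks 4.8 h worse.
- Mean over all randomized, counting 0 h for those sent home: control 22.08 h, FAST 0.36×60 = 21.60 h. FAST is 0.48 h better.
- If children sent home instead contribute an ED stay of *e* hours, the FAST-minus-control difference is 0.04 × (*e* − 12). It stays negative as long as the ED visit is shorter than the 12-hour stay it replaces.

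| Control hospitalized (assumed) | Mean among hospitalized, control vs FAST | Mean over all randomized, control vs FAST |
|---|---|---|
| 30% | 53.6 vs 60.0 h | 16.08 vs 15.60 h |
| 40% | 55.2 vs 60.0 h | 22.08 vs 21.60 h |
| 50% | 56.2 vs 60.0 h | 28.08 vs 27.60 h |

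The planned test uses ranks, but it moves the same way. At 40%, a tenth of control stays (0.04/0.40) are the averted short ones. If all other stays exceed 12 h, the chance that a FAST stay exceeds a control stay, counting ties as half, is 0.10 + 0.90 × 0.5 = 0.55.

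This example is stark, since every averted stay lies at the bottom of the distribution. Simulations with overlapping lognormal stays (30–50% admitted, 15–20% of all children having short stays, 2–4 points averted, all assumed) gave medians among the hospitalized 0.5 to 5.3 h longer with FAST. The result was p<0.05 in 9–59% of trials, while mean stay over all randomized fell by 0.3 to 0.8 h.

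**4. Time to CT (assumed inputs).** Potential scan times are lognormal with median 120 min and log-SD 0.6. Children above a risk threshold are scanned, FAST drops the lowest-risk scans (34% to 30%), and no child's time changes. With P the chance that a FAST time exceeds a control time, z = (P − 0.5)/√[(739 + 652 + 1)/(12 × 739 × 652)] = (P − 0.5)/0.0155, and the chance of p<0.05 is Φ(|z| − 1.96) + Φ(−|z| − 1.96).

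| Strength of risk–time correlation | Medians if higher risk is scanned sooner, control vs FAST | Medians if scanned later, control vs FAST | Distance of P from 0.5 | Chance of p<0.05 |
|---|---|---|---|---|
| 0.3 | 98.9 vs 97.5 min | 145.6 vs 147.7 min | 0.0071 | about 7% |
| 0.5 | 87.1 vs 85.0 min | 165.3 vs 169.5 min | 0.0127 | about 13% |
| 0.7 | 77.1 vs 74.5 min | 187.0 vs 193.6 min | 0.0203 | about 26% |

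P comes from numerical integration of this model. By symmetry the chance is the same for either sign of the correlation. The shift runs from 1.4 to 6.6 minutes, in either direction.

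**The case against.** Several points on the other side stand.

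- **The safeguards are partly in place.** Hospitalization and stay are listed as one paired secondary outcome, and both the hospitalization and CT proportions use all participants. A careful reader would see averted admissions beside the longer conditional stay. That helps interpretation but does not make the conditional test a randomized one.
- **The efficiency question does not rest on these two outcomes.** ED length of stay comes first among the secondary outcomes and is defined for every child. It would be wrong to infer that the trial has no sound time outcome, or that its main result is at risk. The article says the secondary outcomes are not its focus.
- **An effect on admission is assumed.** The documents neither predict nor report one. The earlier single-center trial with the same criteria found no difference in CT use; if that recurred, there would be little selection on CT.
- **CT timing.** A reader might infer that averting low-risk scans must make FAST look faster. The documents do not say whether higher-risk children are scanned sooner, and the table shows the sign turning on exactly that. The shift is small either way.
- **The analysis set is partly inferred.** The methods compare stays between participants in the two arms, and an analysis plan not shown might assign ranks to children without a value. But the definitions fix stay as a variable of the hospitalized and CT time as a variable of the scanned, and nothing in the article assigns the others a value.

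**Conclusion.** The point holds as one of design: as written, both tests compare subsets formed after randomization.

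For hospital stay the consequence can be a reversed sign. This requires that FAST averts mainly short stays, and the size depends on inputs the documents do not give. If FAST instead added short observation stays, the arms in the calculation swap and a cost would read as a benefit.

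For time to CT the consequence at a 4-point difference is a shift of a few minutes, with the false-positive rate raised from 5% to about 7–26% in this model and no predictable direction.

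The primary CT comparison, the sample size and ED length of stay are unaffected. The change is worth making because it is cheap and the trial is still enrolling.

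**What to change.** - **Stay.** Make the between-arm test a comparison, in all randomized children, of time from ED arrival to final discharge from the ED or hospital. Children discharged from the ED contribute their ED stay.
- **CT timing.** If it is compared between arms, use the cumulative incidence of CT from ED arrival in all randomized children, with ED disposition without CT as a competing event. If scans after admission but within 24 h are to count, only ED discharge without CT should compete; the rule should follow the window used for the CT proportion.
- **Conditional summaries.** Report the medians among the hospitalized and among the scanned descriptively, without a test, beside the hospitalization and CT proportions.

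The cost is some wording and a little programming, since the needed times are already measured from ED arrival. There is a downside: the all-randomized measures mix whether an event occurs with when it occurs, and they partly overlap with ED length of stay and the CT proportion. That is why the descriptive medians should stay.
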